### Safety

The trial has been designed to reduce participant risk and burden as much as possible, with strict adherence to best practice guidance for all methods. Any adverse events (AEs) reported will be documented with information pertaining to their severity and anatomical location and the CI will classify the AE according to internationally recognised definitions^64^ and promptly report these to the appropriate regulatory bodies and ethics committees as required. Any serious AEs (SAEs) will be immediately reported to the CI, who will assess the relatedness to the intervention. Reports of related and unexpected SAEs will be submitted to the Research Ethics Committee and sponsor (University of Birmingham).

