During the first 4 weeks of the intervention, a research team member will adopt a flexible approach to scheduling supervised sessions, accommodating participant needs. The team member will assist with the physical setup for the arm-crank exercise, as well as provide verbal encouragement and guidance regarding exercise performance. In line with the consensus-based recommendations for exercise research in SCI,^64^ behaviour change techniques such as goal setting and planning with participants to set exercise goals during the session, using exercise logs to help participants track their progress, offering regular, constructive feedback during their exercise sessions and celebration of milestones (eg, completing a session with no breaks) will be implemented. BP will be monitored where individuals report symptoms of low or high BP (eg, light-headedness or headache) before or after exercise sessions during this initial 4-week period. At the start of week 5, participants will begin to transition to autonomous training with the goal to being fully autonomous by the end of week 6. During the transition period, the research team will provide only minimal guidance; for example, when participants struggle to remember proper setup or execution. This ensures that participants can independently perform exercise sessions over weekends when the weekly exercise session frequency increases towards the latter stages of the intervention. The transition from assisted exercise sessions to autonomous training reflects the principles of the self-determination theory,^79^ particularly in the context of autonomy and competence. Participants will be gradually given more control and responsibility over their exercise sessions to foster autonomy. As participants gain confidence and proficiency, the lessened reliance on external assistance promotes a sense of competence in their ability to exercise.

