**Figure 3 F3:**
[figure not shown]
Study flow chart. Following participant identification and initial assessments (**A1**) at MCSI, assessments will be repeated after a period of standard care (which will primarily involve bed rest depending on the severity of injury) (**A2**). Participants thereby act as their own controls. At this point, participants will be randomised to receive either standard of care inpatient rehabilitation (CONTROL) or standard of care inpatient rehabilitation plus 30 min of ACET, 3–5 times per week (ACET INTERVENTION) for 10 weeks, with postassessments (**A3**). 6 months after discharge (~36 weeks) into the community, follow-up HRQOL assessments will be carried out (**A4**). ABPM, ambulatory blood pressure monitoring; ACET, arm-crank exercise training; HRQOL; health-related quality of life; SCI, spinal cord injury.

The A1 assessment serves as a time point for characterising key outcome measures on admission into inpatient rehabilitation, providing a baseline of cardiovascular health. Given the significant adjustments participants face following this life-changing injury, we have streamlined some of the secondary outcome measure assessments between A1 and A2 to minimise participant burden. Therefore, rehabilitation physical activity energy expenditure, 24-hour BP monitoring and motor function assessments will be conducted only once between A1 and A2, as outlined in table 2. The rationale for having both A1 and A2 assessments for the cardiovascular measures and HRQOL questionnaires is twofold: (1) to gauge any variability or changes in responses between the time close to admission (A1) and the adjustment to their new injury (A2; for example, following initial standard of care therapy sessions) and (2) to establish multiple baselines for these outcome measures, thereby allowing participants to serve as their own controls and capturing the inherent variability in these outcomes.

**Table 2 T2:** Schedule of enrolment, interventions and assessments

Study procedures	Screen	Baseline(A1)	A1–A2	Preintervention/randomisation(A2)	Training sessions	Final week	Postintervention(A3)	Community follow-up(A4)*
Visit (V)	V1	V2	V2/V3	V3/V4	V4/V5–V45/V46	V46/V47	V47/V48	V48/V49
Eligibility								
Informed consent	X							
Medical history/demographics	X							
Changes in medication/health status				X			X	
Pregnancy screening	X							
International Standards for Neurological Classification	X						X	

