Autonomic Dysfunction in Spinal Cord Injury	X						X	
Primary Outcome								
Carotid-Femoral Pulse Wave Velocity		X		X			X	
Secondary outcomes								
Blood sampling		X		X			X	
Health-Related Quality of Life Standard Questionnaires		X		X			X	X
Digit Span and Symbol Digit Modalities Test		X		X			X	
Wheelchair Users Shoulder Pain Index		X		X	X(weekly)		X	X
Cardiovascular Ultrasound		X		X			X	
Resting heart rate variability		X		X			X	
24-hour ambulatory blood pressure monitoring			X			X		
Rehabilitation energy expenditure (>3 days of monitoring) and free-living heart rate variability			X			X		
Motor function testing			X				X	
Arm cycle exercise familiarisation			X					
Cardiorespiratory fitness and heart rate recovery				X			X	
Continuous exercise heart rate and episodic (pre/post) Blood pressure monitoring					X(all sessions)			
Feasibility and Acceptability Questionnaire							X	
One-to-one Interview							X	

* For the A4 time point, only Health -Related Quality of Life Questionnaires and WUSPI will be completed.

Cardiorespiratory fitness assessments commence at A2 following a 20 min familiarisation session on the arm-crank ergometer, which will be performed by all participants between A1 and A2 (see table 2). The duration between A1 and A2 will be at least 2 weeks, although this timeframe is flexible based on the clinical needs of the patient. For example, prolonged bed rest may necessitate a longer interval before initiating standard of care rehabilitation due to factors such as fatigue or secondary complications such as pressure sores or urinary tract infections. At A4, occurring 6 months after A3 (ie, postintervention), we will remotely reassess HRQOL outcomes to determine whether there are differences between the ACET and CON groups.

A1, A2 and A3 assessments will be carried out within MCSI at the RJAH. A4 follow-up assessments will be conducted virtually. To ensure fidelity of assessments, the CI and research personnel held initial meetings for standardised training and logistics. Regular executive committee meetings consisting of the CI ([name]), site PI ([name]), site clinical lead ([name]), postdoctoral research fellow ([name]), research nurse, healthcare assistant and other MCSI staff will convene to discuss any data collection issues or safety issues that arise.

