## Discussion

Individuals living with chronic SCI in the UK report being satisfied or very satisfied with their life as a whole and various aspects of their life, but often report challenges related to occupation and physical independence,^133^ highlighting the need to investigate alternative rehabilitation strategies to promote functional independence after injury. Given the high prevalence of detrimental health consequences associated with SCI, the implementation of early and effective therapeutic interventions targeting cardiovascular health is crucial.^54^

Current management of SCI mainly focuses on functional rehabilitation and does not include any formal prescription of an aerobic exercise programme to minimise cardiovascular dysfunctions and CVD risk.^134^ However, initiating an exercise intervention early in the subacute phase of inpatient rehabilitation after SCI (ie, within 12 months) could serve as a preventive measure to mitigate the increased CVD risk associated with SCI.^135^ The outcomes of this study have the potential to provide evidence of whether implementing early cardiovascular-focused exercise interventions in the subacute stage of injury could be a safe and effective approach to prevent secondary complications associated with SCI and enhance independence in performing activities of daily living for individuals with SCI.

The early rehabilitation environment represents the ideal time and location to embed healthy lifestyle behaviours, including upper-body exercise conditioning.^77^ Previous research has demonstrated that moderate-intensity exercise interventions have induced favourable adaptations in untrained individuals with chronic SCI, such as improved functional capacity (ie, cardiorespiratory fitness and peak power output) and a range of HRQOL measures.^66 136 137^ Moreover, these types of interventions may result in reduced healthcare expenses after discharge from inpatient rehabilitation, which can be an average lifetime cost of £1.12 million per SCI case in the UK.^138^ Furthermore, this moderate-intensity exercise intervention has broader implications for addressing mobility issues and mitigating CVD risk in various inpatient groups.

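### Adverse events are recorded as reported, while several research contacts between A2 and A3 are described only for ACET, so arm-level counts of non-serious events risk unequal ascertainment of unknown size

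*Protocol article*

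**What the plan says.** **Capture.** Protocol article, Safety: "Any adverse events (AEs) reported will be documented with information pertaining to their severity and anatomical location". The chief investigator classifies events, and serious events go to the chief investigator immediately. No enquiry common to both arms is described.

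**ACET contact.** Under Arm cycle ergometry training, in the first four weeks "a research team member will adopt a flexible approach to scheduling supervised sessions". From week 5, "participants will begin to transition to autonomous training with the goal to being fully autonomous by the end of week 6". The same section gives a review of adherence every three weeks. Participants discharged early get a home visit, a supervised first home session and a weekly call. Health-related quality of life ties the weekly shoulder-pain index (WUSPI) to the ACET group.

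**Contact in both arms.** Table 2 lists "Changes in medication/health status" at A2 and A3. It also has a final-week visit (ambulatory blood pressure, energy expenditure) and several A3 assessments with no arm restriction. Standard of care gives inpatients at least 15 hours of rehabilitation a week.

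**Blinding.** Under Randomisation, neither participants nor data collectors are blinded.

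**Use.** The Discussion hopes to provide evidence on whether early exercise "could be a safe and effective approach to prevent secondary complications associated with SCI".

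**The concern.** A minor event enters the record only if someone mentions or notices it and passes it to the trial. A participant who meets the research team several times a week, or completes a weekly shoulder-pain form, has more chances to mention a sore shoulder or a dizzy spell than one who does not. If those chances differ by arm, a raw table of non-serious events mixes true differences with differences in opportunity to report. Unblinded staff and participants may add to this, because both know who is exercising.

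What is at stake is the reading of safety. With 42 participants, about 21 per arm, a few events captured in one arm and missed in the other could make ACET look less well tolerated than it is. Within ACET, direct supervision is withdrawn as session frequency may rise, so a time pattern in recorded events would be hard to interpret.

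**Working it through.** The article gives no event rate, capture probability or planned event comparison, so there is no figure of its own to reproduce. The check sets the contacts side by side and then shows what unequal capture could do.

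**1. Contacts described between A2 and the end of the period**

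| Contact | ACET | Control |
|---|---|---|
| Supervised sessions, weeks 1–4; minimal guidance from week 5 | yes | none described |
| Weekly WUSPI up to A3 | yes | none described |
| Adherence review every 3 weeks | yes | not applicable |
| After discharge: home visit, then weekly call | yes | none described |
| Ward rehabilitation, at least 15 h/week while an inpatient | yes | yes |
| Final-week monitoring and A3 assessments | yes | yes |

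The research-team contacts differ by arm. The ward contact and the end-of-period assessments do not.

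**2. ACET sessions by period**

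- Minimum schedule: 10 × 3 = 30 sessions. Weeks 1–4 hold 12 (40%), weeks 5–6 hold 6 and weeks 7–10 hold 12 (40%).
- Full progression: 3×3 + 3×4 + 4×5 = 41 sessions. Weeks 1–4 hold 13 (32%), weeks 5–6 hold 8 and weeks 7–10 hold 20 (49%).
- On the full progression, weekly frequency rises from 13/4 = 3.25 to 5, a factor of 5/3.25 = 1.54.

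These counts describe exposure and supervision. They do not measure event capture.

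**3. Illustration (all capture values are assumptions)**

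Take the same true weekly event rate in both arms. Let capture in ACET be p in weeks 1–4, (p+q)/2 in weeks 5–6 and q in weeks 7–10. Let capture in controls be q throughout.

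Recorded ratio ACET/control = [4p + 2(p+q)/2 + 4q] / (10q). Late/early ratio within ACET = q/p.

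For p = 0.9 and q = 0.5: (3.6 + 1.4 + 2.0)/10 = 0.70; 0.70/0.50 = 1.40; late/early = 0.5/0.9 = 0.56.

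| q (p = 0.9) | ACET/control | Late/early in ACET |
|---|---|---|
| 0.9 | 1.00 | 1.00 |
| 0.8 | 1.06 | 0.89 |
| 0.7 | 1.14 | 0.78 |
| 0.5 | 1.40 | 0.56 |
| 0.3 | 2.00 | 0.33 |

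Now let the continuing ACET contacts hold late capture at r = (p+q)/2, with weeks 5–6 at (p+r)/2. For q = 0.5, r = 0.7: (3.6 + 1.6 + 2.8)/10 = 0.80; 0.80/0.50 = 1.60; late/early = 0.7/0.9 = 0.78. The arm difference widens while the fall over time shrinks.

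**4. A conflict in the monitoring text**

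Arm cycle ergometry training describes blood-pressure checks when symptoms are reported "before or after exercise sessions during this initial 4-week period". Table 2 lists "Continuous exercise heart rate and episodic (pre/post) Blood pressure monitoring" and marks it for all sessions. The two give different accounts of how much is observed in ACET after week 4, and they must be reconciled.

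**The case against.** A reader might infer that controls have no contact, that observation of ACET ends at week 6, and that recorded rates must therefore differ by arm and fall over time. The article does not support this.

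- **Controls are seen.** As inpatients they have the same minimum ward hours as ACET. The final-week visit and several A3 assessments carry no arm restriction. Executive committee meetings that include ward staff discuss safety issues, so ward-detected events have a plausible route into the record in both arms.
- **ACET contact continues.** The weekly WUSPI and three-weekly reviews run on, heart rate is scheduled for every session, and full autonomy by week 6 is a goal for exercise guidance.
- **The direction over time is open.** Rising session volume could push exercise-related events up.
- **No formal event comparison or time trend is planned**, safety is not a listed outcome, and the Discussion sentence is hedged.
- **The article is condensed.** The full protocol may specify how events are elicited.

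Most of this stands, and it limits the claim to a risk of unknown size. Three things remain. The unequal contact schedule is stated in the article and does not depend on what the article leaves out. Ward care does not cover participants discharged within the 10 weeks, which the article expects for some; discharged ACET participants get weekly calls and no equivalent is described for controls. And the Discussion names unblinding, control-group exercise and the single centre as limitations, but not unequal event capture.

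**Conclusion.** The point holds as a risk of differential ascertainment of non-serious events between arms, probably against ACET. Its size cannot be derived from the article. In the illustration the recorded ratio runs from 1.00 (equal capture) through 1.14 and 1.40 to 2.00 as capture outside supervised weeks falls from 0.9 to 0.7, 0.5 and 0.3. It is 1.60 rather than 1.40 at 0.5 if the continuing ACET contacts sustain late capture. These figures assume equal true rates and 0.9 capture under supervision.

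A decline within ACET is possible but not established. The same continuing contacts that widen the arm difference flatten the time trend, and session frequency may rise about 1.5-fold. Serious events, which have their own immediate reporting route, are much less exposed to the problem. The point concerns how safety is reported and leaves the analysis of cfPWV untouched.

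**What to change.** 1. Ask one fixed adverse-event question, worded identically in both arms, at the health-status check already scheduled at A3, covering the whole of A2 to A3.
2. Ask the same question at withdrawal for anyone leaving before A3. This matters because the withdrawal rule for nine consecutive missed sessions can apply only to ACET. An A3-only question would lose those participants' minor events from one arm.
3. Base any between-arm safety statement on those answers plus serious events.
4. Report events found only through ACET contacts (sessions, weekly WUSPI, calls) separately, as within-arm data per session performed, split into supervised and autonomous weeks with the weeks 5–6 transition shown.
5. State the unequal contact as a limitation.
6. Reconcile the two accounts of blood-pressure monitoring around sessions.

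The cost is one question at a visit that already exists, the same question at withdrawal, and reporting text. The downside is up to 10 weeks' recall of minor events by unblinded participants. Recall will lose some events, but the recall period and the wording are then the same in both arms for everyone who reaches A3.

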### Ethics and dissemination

This study was approved by the Wales Research Ethics Committee 2 (REC reference number 22/WA/0329; approved on 9 November 2022) and registered on the International Standard Randomised Controlled Trial Number registry on 5 May 2023 (ISRCTN99941302). For substantial and non-substantial amendments, the sponsor (University of Birmingham) will sign off on any alterations before submission to IRAS. On completion, the CI will notify the relevant parties and study site of any alterations to the study. The data arising from this trial will be submitted for publication and presented at international conferences (eg, International Spinal Cord Society, American Spinal Injury Association, American College of Sports Medicine). People will be notified of the outcomes of the trial via lay press releases or blogs written for UK SCI charities and support groups. Extensive, individualised feedback will be provided to each study participant following the 6-month discharge period.

## Discussion

Individuals living with chronic SCI in the UK report being satisfied or very satisfied with their life as a whole and various aspects of their life, but often report challenges related to occupation and physical independence,^133^ highlighting the need to investigate alternative rehabilitation strategies to promote functional independence after injury. Given the high prevalence of detrimental health consequences associated with SCI, the implementation of early and effective therapeutic interventions targeting cardiovascular health is crucial.^54^

Current management of SCI mainly focuses on functional rehabilitation and does not include any formal prescription of an aerobic exercise programme to minimise cardiovascular dysfunctions and CVD risk.^134^ However, initiating an exercise intervention early in the subacute phase of inpatient rehabilitation after SCI (ie, within 12 months) could serve as a preventive measure to mitigate the increased CVD risk associated with SCI.^135^ The outcomes of this study have the potential to provide evidence of whether implementing early cardiovascular-focused exercise interventions in the subacute stage of injury could be a safe and effective approach to prevent secondary complications associated with SCI and enhance independence in performing activities of daily living for individuals with SCI.

The early rehabilitation environment represents the ideal time and location to embed healthy lifestyle behaviours, including upper-body exercise conditioning.^77^ Previous research has demonstrated that moderate-intensity exercise interventions have induced favourable adaptations in untrained individuals with chronic SCI, such as improved functional capacity (ie, cardiorespiratory fitness and peak power output) and a range of HRQOL measures.^66 136 137^ Moreover, these types of interventions may result in reduced healthcare expenses after discharge from inpatient rehabilitation, which can be an average lifetime cost of £1.12 million per SCI case in the UK.^138^ Furthermore, this moderate-intensity exercise intervention has broader implications for addressing mobility issues and mitigating CVD risk in various inpatient groups.

One of the strengths of this study is that the intervention programme was constructed based on existing evidence and exercise guidelines for individuals living with SCI.^74^ By addressing limitations observed in previous studies during subacute rehabilitation, our study aims to generate high-quality evidence to answer whether early aerobic exercise rehabilitation benefits cardiovascular health outcomes. In contrast to some exercise intervention studies that overlook participant experiences, our trial will assess feasibility and acceptability through postintervention interviews with participants to inform future clinical rehabilitation interventions during the subacute phase of SCI. Such qualitative data will provide contextual information on the views of the participants and staff working at RJAH. Lastly, the double-baseline assessments for some of our outcome measures allow us to better understand the inherent variability of these outcomes in the inpatient setting. However, we acknowledge the limitations of this study. Blinding of participants and the study investigator cannot be performed due to the awareness of the randomised intervention. Nevertheless, data analysts will be kept blind to group allocation, which may decrease the risk of detection bias during the study’s implementation. There is also the possibility that participants in the CON might independently engage in ACET or other physical activity behaviours, which could potentially confound the results. Lastly, study recruitment and procedures will be conducted solely in one SCI Centre, potentially limiting the generalisability of the findings to other centres in the UK. Despite these limitations, the trial will contribute valuable insights to advance our understanding of mitigating CVD risk in newly injured individuals with SCI.
